### Intervention

The implementation strategy for this project was developed based on guidelines by Proctor et al. [28] and informed by the Johns Hopkins Quality and Safety Research Group translating evidence into practice model [40] (Table 2). It involves a comprehensive process of identifying candidates for QIC membership, planning and establishing the QICs, delivery of an evidence-based education package, provision of ongoing clinical and quality improvement expertise, regular financial and other incentives, and facilitation of QIC engagement over 18 months. The QIC model centres the health professional as the experts in their own service context and grants autonomy in enacting and tracking quality improvement activities over time.

**Table 2 Tab2:** Overview of implementation strategy for Agents of Change project, informed by Straus et al. [40]

Implementation strategies	Description
Plan	
Gather information	• Literature review to establish known barriers and facilitators to implementation of evidence-based dementia care • Implementation clinicians conduct local needs assessment and organisational mapping • In-depth interviews with implementation clinicians and management • Establish steering committee with representation from people with dementia and carers to guide project conduct
Select strategies	• Implementation clinicians develop a formal implementation plan • Implementation clinicians develop tailored strategies to overcome barriers
Build buy-in	• Identify and prepare implementation clinicians • Involve organisation managers who confirm the clinicians’ involvement in the project and commitment to support • Involve members of the public (people with dementia and carers) and industry in all phases of the project
Initiate leadership	• Implementation clinicians identified as ‘Agents of Change’ within their organisation • Implementation clinicians establish ‘practice teams’ within their organisation to whom they will regularly report back and gather feedback
Develop relationships	• Build the QICs • Obtain formal research agreements • Develop partnerships between the implementation clinicians, members of the public (people with dementia and carers), industry, expert clinicians, and research team • One face-to-face start-up meeting
Educate	
Develop materials	• Development of MOOC with clinical content and focus on quality improvement in clinical settings • MOOC developed in consultation with people with dementia and carers, industry experts, educational designer • Development of implementation plan pro forma for clinicians • Establish group norms and standards of collaboration • Support for implementation clinicians to develop further site-specific resources
Educate	• Provision of training through seven-module MOOC • Phone orientation meeting with research team and face-to-face start up meeting to begin implementation plan brainstorming • Implementation plan reviewed by a person with dementia and their carer, quality improvement expert, and clinical expert • Support for implementation clinicians to gather feedback from ‘practice teams’ within their organisation • Regular audit and feedback based on clinician self-report and client dyad-report
Educate through peers	• Implementation plan reviewed by QIC peer • Ongoing communications within the QIC via online forums and monthly videoconferencing
Inform and influence stakeholders	• Use mass media, professional organisation newsletters, and industry publications to share information about the project and highlight implementation clinician plans
Restructure	• Implementation clinicians take a lead in quality improvement in their organisations • Site-specific implementation plan may involve restructuring or changes in structure, equipment, or records
Quality management	• Iterative quality improvement process using PDSA cycles • Ongoing peer supervision with subgroup of QIC members • Support for implementation clinicians to gather ongoing feedback from ‘practice teams’ within their organisation • Fidelity checking based on content of clinical interactions (via clinician self-report and patient and client dyad-report) • Monthly QIC meetings in which each clinician will report their plan activity for the month • Revisiting of implementation plan after each monthly meeting with update log; revised plan submitted 6 months after implementation • Reminders • Provision of client tools to increase uptake of best practice (to half of the sites) • Ongoing access to people with dementia and carers and clinical, quality improvement experts throughout implementation and follow-up
Finance	
Incentive scheme	• Implementation clinicians who complete 18 months follow-up receive access up to $1000 stipend to present their work at a meeting or conference • Provision of regular incentives to encourage fidelity (e.g. webinars and other resources, branded materials)

*Abbreviations*: *MOOC* massive open online course, *QIC* quality improvement collaborative

#### Plan

We will build the QIC by developing relationships with implementation clinicians and the managers of their organisations. Organisational support for the implementation clinician will be confirmed with a formal research agreement that will outline the expectations and role of the clinician, the site, and the research team. Detailed interviews with implementation clinicians and management, as well as organisational mapping and local needs assessment, will establish barriers to best practice care, opportunities for improvement, readiness for change, and expectations from the QIC. Implementation clinicians will be identified as change champions within their organisation via internal media and will be encouraged to establish a small team of colleagues with whom they can regularly report back on their project activity and gain feedback. This phase will also include development of partnerships with clinical, quality improvement and industry experts to provide guidance and advice throughout the life of the project. A once-off face-to-face meeting with all implementation clinicians, the research team, and clinical leaders will build buy-in, further develop relationships, and give credibility to the project.

People with dementia and/or carers will be recruited to be involved at all levels of the project including in the senior investigator and management teams, as members of an advisory committee, in intervention development workgroups, and for ongoing implementation clinician support. This involvement is embedded into the implementation strategy and wider project management across the life of the project to avoid tokenism [41] and to capitalise on demonstrated benefits for researchers, ethical and scientific standards, and the wider community [42–44]. Saunders et al. [45] argue that health research is a social process and should therefore be informed by interactions between researchers, research participants, and potential end beneficiaries (especially where the research will directly inform health care, as in this project). Feedback and ongoing support from people with dementia and/or carers are anticipated to contribute to project buy-in, motivation for change, and quality of plans for change among implementation clinicians [43, 46]. Recruitment for this purpose will be conducted separately from implementation sites via peak body and research centre networks. Per Australian guidelines [42], all of those recruited will be reimbursed for the time they spend providing expert advice and oversight.

#### Educate

Education for implementation clinicians will be delivered after a 9-month pre-intervention period and include written resources, webinars, expert feedback, collaboration and peer supervision, and online learning. The main component of the education will be an intensive, eight-module ‘massive open online course’ (MOOC) to upskill implementation clinicians on the clinical evidence base related to occupational therapy for people with dementia, physical activity for people with dementia, or carer support. The MOOC will focus on quality improvement techniques in clinical settings. Implementation clinicians will be guided through the development of an associated implementation plan unique to their service context and informed by service gaps and barriers and facilitators to improvement identified during the planning phase. The MOOC will be co-designed with people with dementia and carers to ensure it reflects their needs and experiences. Input will also be sought from clinical, aged care industry, quality improvement, and educational design experts to ensure it is rigorous, up-to-date, and effectively facilitates learning. Implementation clinicians will have access to people with dementia, carers, and clinical and quality improvement experts to review their plan and provide feedback. A peer review process will also allow implementation clinicians to give and receive feedback from another member of their QIC.

#### Restructure

Through their work to develop and implement a quality improvement activity to be delivered in their service, it is anticipated that the implementation clinician will become recognised as a clinical leader in their organisation. Their plan may include some restructuring of organisation policies, service delivery, resources, records, or staffing.

#### Quality management

Once reviewed, clinicians will implement their plan and participate in monthly virtual meetings with their QIC to benchmark and brainstorm strategies to overcome any noted roadblocks. They will iteratively review and update their plans using PDSA cycles [47] with support from people with dementia and carers and clinical and quality improvement experts. Clinician reports of the consultation will be audited, cross-referenced with client dyad reports, and anonymously fed back to facilitate self-assessment.

#### Finance

Travel costs for clinicians to attend the face-to-face meeting will be covered by the project. Regular incentives will be provided to encourage clinicians to remain engaged with the project and their implementation plan, including staggered provision of written resources (e.g. books, peer-reviewed journal articles), branded materials, gift cards, and exclusive webinars. The work by implementation clinicians to make clinical improvements will be highlighted by the research team in collaboration with their organisation in both mass media and internal organisation media. At the completion of their 18-month project commitment, implementation clinicians will have access to a $1000 stipend to attend a meeting or conference of their choice to present their work.

### Outcomes

The outcomes and measures that will be used for this study are presented in Table 3. Outcomes of interest relate to guideline adherence, implementation of the QIC methodology, service level effectiveness and harms, and client dyad outcomes.

**Table 3 Tab3:** Project outcomes

Outcome domain	Details of measurement
Guideline adherence	
Exercise guideline adherence	Full adherence when: a) Clinician checklist explicitly references a discussion about current physical activity levels, and; b) Specific needs and barriers to physical activity are identified, and; c) Treatments/strategies recommended are clinical indicated based on needs/barriers, and; d) A written treatment plan for physical activity or exercise is provided to the person with dementia
Occupational therapy guideline adherence	Full adherence when: a) Home environment assessment has occurred (where applicable), and; b) Clinician checklist explicitly references identification of primary concern/s of person with dementia and carer, and; c) A written treatment plan to address needs of person with dementia and carer or give specific advice about suitable activities (that are tailored, of interest, and match capabilities) is provided
Carer support guideline adherence	Full adherence when: a) Clinician checklist explicitly references that the needs of the carer have been discussed during the consultation, and; b) Clinician checklist explicitly references clinically indicated provision of information about programs providing respite for the carer and/or other carer support services, and; c) A written treatment plan detailing key carer concerns and strategies to manage these is provided
Implementation	
Uptake	• Exposure: the extent to which clinicians use the materials and online training course • Initial use: initial changes in adherence to guideline recommendations
Sustainability	• Continued changes in adherence to guideline recommendation.
Feasibility	• Recruitment: attraction of implementation clinicians and participating organisations • Consent rate for people with dementia and their carers agreeing to be contacted for follow-up • Maintenance: involvement in the program and contribution to data collection • Withdrawals
Acceptability	• Interviews with implementation clinicians regarding participation in the program and the acceptability of the intervention and process • QIKAT-R tool: a three-item tool that identifies the skills and knowledge of the implementation clinicians in quality improvement (i.e. how well they can assess the need for change and identify appropriate strategies) • NOMAD tool: a validated method of exploring why clinicians change their practice and why they do not, and this is a key aim of process evaluation.
Fidelity	• Fidelity determined via checklists on the content of clinician-patient/carers interactions. Data captured via clinician self-report checklist and phone call surveys with patients and carers
Penetration	• Context: information about the sites and funding models, as well as the different types of clinicians (professional background, level of seniority, and type of role). • Reach: does the project reach a variety of different sites and people with dementia and carers
Costs	• Calculation of costs of providing the intervention (personnel, technology, stipends, development and distribution of educational materials) and in-kind contribution required for each site estimated using a ‘bottom-up’ micro-costing approach. • Willingness to pay questionnaire
Impact of involvement of people with dementia and carers at all levels of the project	• Impact of involvement of people with dementia and carers on intervention quality, success • Expectations and experiences of people with dementia and carers involved in the project
Service	
Safety	• Implementation clinicians will record any adverse events and discuss any unintended consequences
Client	
Satisfaction	• Amended version of the Patient Satisfaction Questionnaire Short-Form
Function/QOL	• DEMQOL assesses the quality of life of clients with dementia (exercise and OT groups only) • ZBI assesses the burden experienced by carers of people with dementia (‘carer support’ group only)

*Abbreviations*: *DEMQOL* Dementia Quality of Life Questionnaire, *MOOC* massive open online course, *NOMAD* questionnaire tool based on Normalisation Process Theory, *OT* occupational therapy, *QIKAT-R* Quality Improvement Knowledge Application Tool Revised, *QOL* quality of life, *ZBI* Zarit Burden Interview

#### Guideline adherence

The primary outcome of the implementation evaluation is changes in guideline adherence over time. Guideline adherence will be assessed using monthly checklists completed by implementation clinicians about their consultations with people with dementia and/or carers. Clinicians will complete the checklists for the first ten consecutive consultations each month. Clinicians will be asked to provide a ‘snapshot’ of the consultation including its purpose, content, and outcomes. A process for guideline adherence scoring was modelled on methods used in Kortekaas et al. [48] and van Fenema et al. [49]. Key indicators of guideline adherence were developed in consultation with clinical and consumer experts (see Table 3). Two independent researchers will rate whether the practice reported by the clinician was inadequately (− 1), partially (or unclear; 0), or fully adherent (+ 1) to the relevant recommendation. In cases of disagreement, a third external clinical academic will be contracted to make a final decision. A follow-up phone interview with a random selection of client dyads each month up to 5 weeks after the consultation will be used to verify these reports, and ‘agreement’ between the client dyad and clinician will be assessed. Phone interviews will be conducted by the study team with both the person with dementia and their carer where possible, or just the carer where they are directly participating as a client of clinicians in the ‘carer support’ or the person with dementia is unable to participate in a phone call. People with dementia who attend the consultation alone (including those who live in long-term care) will not be contacted by phone. Interviews will gather perspectives from the dyad or carer about their recollection of the consultation and the extent of guideline adherence from their perspective. Clinician and client dyad data will be triangulated with field notes from QIC meetings, online message board participation, and other contact with the research team.

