**Methods:**

This project will employ an interrupted time-series design with process evaluation to assess the impact, uptake, feasibility, accessibility, cost, and sustainability of the QICs over 18 months. Thirty clinicians from across Australia will be invited to join the QICs to build their capacity in leading innovation in dementia care. Clinicians will participate in a training program and be supported to develop and implement a quality improvement project unique to their service context using plan-do-study-act cycles. Regular online meetings with their peers in the QIC will facilitate benchmarking and problem-solving. Clinicians will describe their practice via monthly checklists, and guideline adherence will be determined against a set of defined criteria. Phone interviews with up to 180 client dyads will be used to assess satisfaction with care and client outcomes. Clinician interviews and field note data will be used to explore implementation and costs. Involvement of people with dementia and carers will be embedded in the study design, conduct, and reporting, in addition to clinical and industry expertise.

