Client dyads will be existing patients with dementia and/or their carers within the caseload of the implementation clinician at the implementation site. Strict inclusion criteria will not be applied, and implementation clinicians will be asked to use their judgement; eligible people with dementia will be any client with a diagnosis of dementia (or suspected dementia) who attends a consultation with or without a carer. Carers will be any person attending the consultation who provides substantive care for a person with dementia and identifies as a carer. Implementation clinicians will complete the checklists about their consultation with each person with dementia (or carer, or dyad, where applicable) they see and return these to the study team. They will also ask for verbal assent (from both members of the dyad, where applicable) to pass contact details onto the study team for the purposes of two follow-up phone interviews. The study team will randomly select one dyad (per clinician) from among those assenting each month to receive these phone interviews (details below), for a total of 180 dyads.

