### Analysis

#### Quantitative analysis

Guideline adherence and client outcomes over time will be evaluated with a segmented regression analysis using the PROC NLIN function of SAS version 13.2 [63]. This technique uses modelling to draw conclusions about an outcome (in this case guideline adherence) across distinct segments of time (in this case, before and after quality improvement implementation) [64]. Data points for the time series will be the extent of guideline adherence each month over 18 months. Potential confounding variables will be fitted as covariates, and the most parsimonious model will be determined via stepwise backward elimination. The hypothesised outcomes of interest for this study are level and trend changes reflecting increasing adherence to the relevant guideline recommendation after the intervention (post-education quality improvement implementation) and over the 18 months. We will also calculate the counterfactual value and its proportionate distance from the actual estimated value [65]. The PROC AUTOREG function will be used to control for autocorrelation [63].

The sample size calculation for segmented regression analysis is related to the estimated number of time points at which data will be recorded. It is necessary to have enough time points before and after the intervention. This study incorporates 18 months of data collection (9 months pre-intervention and 9 months post-intervention) and is powered at 83% to detect a minimum 15% change in guideline adherence based on an estimated effect size of 1, autocorrelation of 0.3, and *α* = 0.05 [66]. This change in guideline adherence was used for power analysis based on literature suggesting an average of 10–15% improvement in adherence from traditional guideline dissemination activities [7]. Per recommendations from Wagner et al. [65], clinicians will submit up to ten checklists for each data point in the time series (for a total of up to 300 checklists each month) to achieve an acceptable level of variability of the estimate at each time point. The study design therefore meets the criteria for a robust interrupted time-series [67].

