Despite these strengths, the approach for this study has some important limitations. First, the inclusion of a control group was considered unethical because clients would be deprived of best-practice care, and engaging clinicians to provide data without any intervention would be difficult. Effects occurring at the same time but separate to the intervention will not be separated and controlled for, threatening validity. Nonetheless, even without a control group, segmented regression analysis makes multiple assessments of the outcome and therefore addresses important threats to internal validity. Second, the primary outcome measure (guideline adherence) will be self-reported by the implementation clinicians and is therefore vulnerable to a responding bias. The triangulation of data from client dyad phone calls will help to address this problem, and adherence (according to the criteria described in Table 3) will be independently judged by two members of the research team and an external third party where needed based on clinician reported ‘snapshots’ of the consultation. Nonetheless, some responding bias may still exist. Third, a selection bias may be present in the participating implementation clinicians. The ‘opt-in’ approach to recruitment will likely lead to a group of passionate and engaged clinicians who may not represent the wider population of clinicians working with people with dementia and their carers. Finally, there are some limitations associated with segmented regression analysis. These models assume a linear trend in the outcome within each segment, but this may not hold over longer intervals [65]. Segmented regression analysis also does not allow for statistical controlling of individual-level covariates. However, these covariates will only become confounding where they both predict the outcome and change in relationship to the time of the intervention. No such covariates are anticipated.

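### Research-team members score the primary outcome with no stated masking to period, and the client-dyad check cannot detect rater drift

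*Protocol article*

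**What the plan says.** **Rating.** Under Outcomes, Guideline adherence, clinicians complete checklists for their first ten consecutive consultations each month. "Two independent researchers will rate whether the practice reported by the clinician was inadequately" (−1), partially or unclearly (0), or fully (+1) adherent. A third, external academic decides where the two disagree. The Discussion, where it sets out safeguards against self-report bias, says that adherence "will be independently judged by two members of the research team".

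**Criteria.** In Table 3 each of the three definitions of full adherence includes at least one item that turns on what was written down. For exercise, the first is "Clinician checklist explicitly references a discussion about current physical activity levels". All three also require a written plan.

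**Timing.** Education is delivered after a 9-month baseline (Educate) and covers the same clinical topics. Under Quality management, clinician reports are audited, compared with dyad reports and fed back anonymously. The Discussion explains why there is no control group.

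**Check on the reports.** A random sample of dyads is telephoned each month, and their agreement with the clinician is assessed. On self-report bias the Discussion says: "The triangulation of data from client dyad phone calls will help to address this problem". It concedes that some bias may remain. On the size of the sample, Participants says "The study team will randomly select one dyad (per clinician) from among those assenting each month" and gives a total of 180.

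**The concern.** In an uncontrolled interrupted time series, anything that changes the measurement at the interruption looks like an intervention effect. Two routes are open here.

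- **Reporting.** Clinicians taught about a topic, and given feedback on their reports, may record more of what they already did. An item that used to be unclear (0) then becomes full (+1) with no change in care.
- **Rating.** Raters who know that a checklist comes from after the training may read borderline entries more favourably.

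The external academic sees only disagreements, so drift shared by both raters never reaches adjudication. The Discussion treats self-report bias as a general limitation. It does not take up bias that changes at the break, which is the kind that would distort the level and trend estimates. The conclusion on the primary aim is at stake.

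**Working it through.** **Inputs from the article**
- Clinicians: "Thirty clinicians from across Australia will be invited to join the QICs".
- Time points: "9 months pre-intervention and 9 months post-intervention", so 18 months.
- Checklists: "for a total of up to 300 checklists each month".
- Target: a minimum 15% change, read here as 15 percentage points in the share of checklists scored fully adherent (my reading; the article does not say).
- Dyads: one per clinician per month, total 180 (Participants).

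**Assumptions (no figure in the article)**
- Share of checklists scored 0: 20 to 60%, with 40% as the middle value.
- Share of those that move to full through documentation or leniency alone: one quarter.
- Clinician-dyad agreement before the intervention: 80%, range 60 to 90%.

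**Step 1. The stated dyad total.** 30 clinicians × 18 months × 1 dyad = 540, not 180. A total of 180 would need 6 months of sampling (180 / 30) or 10 dyads a month (180 / 18). Against 300 × 18 = 5,400 checklists, 180 is 3.3% and 540 is 10%.

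**Step 2. How small a shift matters.** 15% of 300 is 45 checklists a month, or 1.5 of each clinician's ten. Under the assumptions, the artefact is (share scored 0) × (share upgraded):
- 0.20 × 0.25 = 5 points
- 0.40 × 0.25 = 10 points, two thirds of the target
- 0.60 × 0.25 = 15 points

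**Step 3. Precision of a pre/post change in agreement.** The 95% half-width is 1.96 × sqrt(2 × p × (1 − p) / n), with n dyads per period and p = 0.80:
- 180 dyads, n = 90: 1.96 × sqrt(0.32 / 90) = 11.7 points
- 540 dyads, n = 270: 1.96 × sqrt(0.32 / 270) = 6.7 points

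**Step 4. Power to see a 15-point fall in agreement** (two-sided 5%). With p1 = 0.80, p2 = 0.65 and mean 0.725, power is Φ of (0.15 − 1.96 × sqrt(2 × 0.725 × 0.275 / n)) / sqrt((0.80 × 0.20 + 0.65 × 0.35) / n).
- n = 90: (0.15 − 0.130) / 0.0656 = 0.30, power 62%
- n = 270: (0.15 − 0.075) / 0.0379 = 1.97, power 98%

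Over baseline agreement of 60 to 90%:

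| Dyads per period | Power |
|---|---|
| 90 (180 in all) | 52 to 76% |
| 270 (540 in all) | 94 to 99.6% |
| 30 (one QIC, 180 in all) | 21 to 33% |

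Clustering by clinician is ignored; an assumed design effect of 1.2 lowers the first two rows to 45 to 68% and 89 to 99%.

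**Step 5. What the check can see.** It compares the dyad with the clinician. The rater's score does not enter, so no sample size and no split by period lets it detect rater drift. For reporting change the direction is ambiguous: if care was given but under-recorded before training, fuller recording would raise agreement. If clinicians begin to over-record, agreement would fall.

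**The case against.** The strongest reply is that this is a condensed article. Silence on masking, rating order or a split by period may be filled by the full protocol or analysis plan, and monthly dyad sampling already permits a split. That stands: the article does not say that raters know the month, and it does not say that agreement is pooled over periods. The point therefore rests on what the article does describe. It names its safeguards against bias, and those safeguards do not deal with a shift at the break.

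The plan also has real protections. Criteria were set with clinical and consumer experts, unclear practice scores 0, a written plan is required for full adherence, disagreements go outside the team, and residual bias is admitted. These limit rater discretion but do not remove it. Whether a strategy is clinically indicated remains a judgement, and fuller documentation passes through all of them.

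Three stronger readings are tempting, and the documents do not support them.
- **That bias could explain the whole effect.** Constant bias produces no level or trend change, and a steady linear drift is absorbed by the pre-intervention trend. The middle assumption gives 10 of 15 points. Only the upper assumption reaches 15, and its inputs are not from the article.
- **That the raters deliver the intervention.** Table 1 says that the project team supports the QICs, and the Discussion says that the raters belong to the research team. Neither says that they are the same people.
- **That the dyad sample is simply too small.** That is arguable at 180 and wrong at 540, and the article supports both numbers.

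**Conclusion.** The concern holds in a limited form. The primary outcome is partly a matter of judgement, scored by research-team members from self-report, with no stated masking to period. A shift in documentation or rating at the interruption could contribute to the estimated effect, and segmented regression without a control cannot separate it from a real change in care. Nothing in the article shows that such a shift will occur. The 5 to 15 points are an illustration resting on the assumed share of unclear checklists and the assumed quarter upgraded.

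The dyad check is a partial defence. It says nothing about raters, and its value on reporting depends on an unresolved number: about ±12 points at 180 dyads or ±7 at 540, assuming 80% agreement and an even split between periods. The conflict between 180 and the monthly rule is the firmest error here.

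**What to change.** 1. For the primary analysis, remove date, clinician and QIC stage from each checklist. Have the same two raters score the checklists in random order across pre- and post-intervention months, separately from any ratings used for ongoing feedback. If rating has begun, stored checklists can be re-scored this way.
2. Report clinician-dyad agreement for each period, with a confidence interval for the change, and present dyad-reported adherence beside the primary result. The latter helps where the direction of a change in agreement is ambiguous.
3. Reconcile the 180 dyads with the rule of one per clinician per month, and state the number expected in each period.

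**Cost.** Data handling and one added analysis, with no new raters. Some checklists may be scored twice if feedback needs immediate ratings. Items 1 and 2 need no new participants; item 3 would need more interviews only if the monthly rule is the one kept. Masking may be incomplete where the content of a checklist reveals the period, and the report should say so.
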